## Abstract

**Background:**

Patients with major depressive disorder (MDD) often experience relapses despite regular treatment with pharmacotherapy and psychotherapy. Further, long waiting lists and more demand than treatment capacity characterize ambulatory settings. Mindfulness-based interventions proved to be effective in relapse prevention in MDD. Next, mindfulness-based interventions in the form of free mobile applications can be an effective augmentation of the treatment as usual and can fill a gap in ambulatory care.

**Objective:**

Given this background, the aim of this randomized controlled study is to assess the effectiveness of additional MBI via a mobile app on the symptom severity and stress levels, compared to treatment as usual.

**Methods:**

A total of 140 individuals with MDD will be randomly allocated to the intervention or control condition. The intervention consists of the daily use of the mindfulness mobile application Headspace for thirty days (up to 10 minutes a day). The control condition will be treatment as usual. At baseline and four weeks later, the following key outcome dimensions will be assessed: self-rated (Beck Depression Inventory) and experts’ rated symptoms of MDD (Hamilton Depression Rating Scale); secondary outcome variables will be blood pressure, heart rate, and respiratory rate and changes in tobacco and alcohol consumption and medication as a proxy of perceived stress.

**Results:**

This study was funded in February 2021 and approved by the institutional review board on April 15, 2021, and it started in May 2021. As of December 2021, we enrolled 30 participants. The findings are expected to be published in spring 2023.

**Conclusions:**

We hypothesize that compared to the control conditions, individuals with MDD of the mobile app-condition will have both lower self- and experts’ rated symptoms of MDD and more favorable stress-related levels. While the risk for medical events is low, the immediate benefit for participants could be a decrease in symptom severity and reduction of the stress level.

**Trial Registration:**

Clinical Trials.gov NCT05060393; https://clinicaltrials.gov/ct2/show/NCT05060393.

**International Registered Report Identifier (IRRID):**

DERR1-10.2196/33423

## Introduction

Major depression disorder (MDD) is a global, serious, and life-shortening disease, affecting about 300 million people worldwide and the main cause of disability-adjusted life years caused by mental diseases [1-3]. The limited capacities in ambulatory care and the increasing mental health needs request innovative, cost-effective interventions [4,5]. During the last decade, research has focused on cost-effective internet-based interventions as add-ons to existing services for individuals with MDD. Such interventions can potentially reduce the gap between the need and provision of psychiatric treatments, though being effective [6-8]. Recently, the need for remote psychological, psychiatric, and internet-based interventions in the mental health sector further increased during the worldwide COVID-19 pandemic and the health-related lockdown measures [9-11]. Accessible strategies can be an effective option to enhance mental health response capacity [12,13].

Mindfulness-based interventions (MBIs), such as mindfulness-based stress reduction or mindfulness-based cognitive therapy, have received considerable attention in modern psychotherapy because of emerging evidence regarding their efficacy in different clinical populations [14-19]. MBCT can both decrease depressive symptoms of a current depressive episode and avoid relapses in individuals with MDD [20-23]. The effects are comparable to those of other cognitive behavioral therapies [24-27] and showed favorable effects if used as an adjunct therapy to treatment as usual (TAU) [28-31]. There is growing evidence that web- and computer-based stress interventions can be effective in reducing stress, depressive, and anxiety symptoms [32-34].

In a study comparing internet-based psychological interventions in primary care, MBIs were effective in both decreasing depressive symptoms and increasing well-being compared to healthy lifestyle psychoeducational program of positive affect promotion [4] and compared to the waitlist control group [35].

As regards mobile applications, these may contribute to closing the treatment gap for depression by reaching large populations at relatively low costs [36]. There is evidence of positive effects of mindfulness-based mobile applications on well-being, stress level, affect, work engagement, irritability, mind wandering as well as sleep quality in different study populations [37-43]. Eight randomized controlled trials using a mindfulness-based app as an intervention group are reported in more detail in Table 1. The intervention period differed from 14 days up to eight weeks (median 28 days).

**Table 1 table1:** Summary of randomized control trials using mindfulness-based mobile applications.

Author/year	Intervention (intervention group)	App	Control group	Study population	Outcome/psychometry	Results
O`Donnell [37], 2020	10 min a day over 30 days	Insight Timer	Wait-list control group	General adult population	Generalized Anxiety Disorder 7 (GAD-7); well being	Not available yet
Huberty [38], 2019	10 min a day over 56 days	Calm	Wait-list control group	College students	Stress, well-being, mindfulness, sleep, alcohol consumption, physical activity	Significant effects in all measured parameters in the intervention group
Möltner [39], 2017	Daily over 14 days	7Mind	Waitlist control group	Employees	Mindfulness, work engagement, job satisfaction, emotional exhaustion, emotional intelligence, innovation and creativity, and self-efficacy.	Significant effects in all measured parameter in the intervention group
Economides [40], 2018	10 min a day over 14 days	Headspace	Audiobook about mindfulness	General adult population with no history of psychiatric disorder	Stress-level, irritability, affection/Stress Overload Scale, Scale of Positive and Negative Experience (SPANE)	Significant reduction of stress level, irritability, significant changes in SPANE score in the intervention group
Howells [41] 2015	10 min a day over 14 days	Headspace	Catch Notes	Facebook and LinkedIn users	The Satisfaction with Life Scale, Flourishing scale, Positive and Negative Affect Scale, Center for Epidemiologic Studies Depression Scale (CESD)	Significant increase in positive effects in the intervention group
Bennike [42] 2020	10-20 a day over 28 days	Headspace	Cognitive training	General adult population with no history of psychiatric disorder	Mind wandering, Sustained Attention to Response Task (SART)	Sign. reduction of mind wandering in the intervention group
Lim [43] 2015	21 days	Headspace	Cognitive training	Students	Compassion	(not significant) increase of compassion in the intervention group
Ly [44] 2014	3-30 min a day over 56 days	App developed for the clinical trial	Behavioral activation via an app developed for the clinical trial	Patients with MDD (Major depression d isorder)	Symptom severity (Beck Depression Inventory II [BDI-II], Patient Health Questionnaire-9 [PHQ-9])	No significant differences between the intervention and the control group

In 4 of the 8 studies, the mindfulness-based intervention was delivered via the app Headspace, probably due to previous findings and a high score in the mobile application rating system [45], making this mobile app promising for further research. The application was brief and easy to use, free to download, and accessible via smartphones globally [41]. Users who sign up for the free trial have access to one of three guided foundation courses, titled “Basics.” There are 10 free sessions in each “Basics” course.

However, and surprisingly, from the reviewed studies, only one study targeted 40 individuals with MDD [44]; the results indicate comparable effects of a mindfulness-based app and behavioral activation via a major depression app.

Given this background and given the scarcity of app-based MBIs in individuals with MDD, the aim of this study is to examine the effects of a mindfulness-based mobile application (Headspace) on the symptom severity and physiological effects in participants with MDD in the real daily clinical practice as an adjunct therapy to the TAU.

The following hypotheses are formulated: first, following Howells et al [41], we assume that compared to a control condition, individuals in the intervention group will achieve a decrease in depressive symptoms. Second, following Huberty et al [38] and Economides [40], we expect a reduction of the stress level in the intervention group compared to the control group. For the following reasons, we hold that this study is of both practical and clinical importance. First, apps allow an individually tailored and self-paced intervention to improve symptoms of MDD and stress; second, such interventional add-ons improve individuals’ self-management and self-responsibility; third, interventional add-ons are easy to use, follow, complete, and monitor, allowing the user to get motivational-enhancing feedback; fourth, such apps provide easy-to-manage data to further improve the dialogue between the user and health care experts; fifth, once a person is accustomed to using the app, the odds are much higher than the person continues to use the app and the appropriate exercising long term.

## Methods

### Aims

The aim of this study is to assess the efficacy of a mindfulness-based mobile application (Headspace) on the symptom severity and the stress level measured by physiological parameters in patients with MDD when compared to a control group. We assume a decrease of the symptom severity, measured by the Beck Depression Inventory II (BDI-II) and Hamilton Depression Rating Scales (HDRS), in the intervention group compared to the waitlist control group. Furthermore, we hypothesize that the stress level assessed by heart and respiratory rate as well as the blood pressure will be lower in the intervention group compared to the control group.

### Study Design

This study will be a single-center, open-label and randomized wait-list-controlled trial, which will take place at the University Psychiatric Clinics (UPK) Basel (Switzerland).

Participants will be randomly allocated to two conditions: (1) MBI mobile application Headspace+ TAU (intervention group) and (2) waitlist + TAU (control group). They will be assessed at baseline and 30 days after baseline (study end). The study flowchart is presented in Figure 1 The study started in May 2021.

**Figure 1 figure1:**
[figure not shown]
Flowchart study design.

The study protocol will be introduced to all participants, the name of the mobile application is not to be communicated in the first step. Previous experience with mobile applications for health will be assessed in all subjects prior to randomization. Randomization is performed by the project leader by using a computer-based randomization algorithm, performing the randomization allocation (ratio 1:1). Each new participant of the study will receive a participant number that corresponds to the following treatment number.

At baseline, participants will complete a series of questionnaires covering sociodemographic and treatment-related information, along with a self-rating (ie, BDI-II) of current symptoms of MDD. An expert will perform a thorough clinical-psychiatric interview and rate participants’ symptoms of depression (ie, HDRS). To assess the current psychophysiological stress response at baseline conditions, a nurse will measure participants’ heart and respiratory rate and blood pressure.

Next, participants will be informed about the study condition assignment. Participants of the control condition will have no additional task to their TAU instruction. Participants of the intervention group will be introduced to the Headspace app and its handling. The necessary timeframe of the baseline assessment will be around 60 minutes.

The intervention group will be required to download the mobile application Headspace and start their daily usage in addition to their TAU (as explained in the “Intervention” section).

Regarding the control group, there will be no intervention planned. The control group will receive the same TAU as the intervention group during inpatient treatment. Participants of both groups will be supported in their outpatient treatment after discharge as usual. Compared to the treatment group, the control group will not be told about the application and its use but will be held on a waitlist. The control participants will be instructed to undergo their TAU (eg, private practice therapist), whereby they will be asked to come to the visit at measurement time T1 after 30 days (see the time points in Table 2).

At T1, both groups will undergo the same procedures as they did at baseline (maximum 60 min). Following the visit, the name of the mobile application will be communicated to the participants of the control group so they can use it after the end of the study as needed.

**Table 2 table2:** Study timeline.

	Time points (days)		
		Baseline (T0)	T1
	–7 to 0	0	+30
Discharge (if inpatients)	√		
Inclusion/ exclusion criteria checked	√		
Signed written informed consent	√		
Medical history, medication	√		
Participant characteristics	√		
Randomization	√		
Visit T0 (baseline)		√	
Visit T1 (study end)			√

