### Participants and Recruitment

In total, 140 patients should be recruited (70 for the intervention and control group each).

Inclusion criteria: inpatients or partial inpatients (day clinic, at least 18 years old, before discharge to ambulatory care as well as outpatients, all diagnosed with MDD according to the International Classification of Diseases. All participants must have a smartphone and be generally willing to download and use a mindfulness-based app for at least 30 days.

Exclusion criteria: Acute suicidality, dementia, acute substance dependency, psychotic, schizophrenic, or schizoaffective disorders, serious health conditions like unstable cardiovascular, heart, lung, endocrine or neurological disorders, and momentary use of Headspace.

The study will be brought to the attention of potentially eligible patients of the UPK through their health care providers at UPK and through the study flyer. If they show interest in participating, the patients will receive a document with all the required information regarding the study in order to give their informed consent. After the patients sign the form of consent, it will take between 1 to 7 days until they will get scheduled for their first appointment. This will give them an adequate amount of time to consider their participation carefully. Participants will be informed about the scope and procedure of the study. Their written informed consent will be obtained.

The participants can be withdrawn from the project for any of the following reasons:

At their own request (withdrawal of consent)In case of nonadherence to the study protocol (if participants use the app on less than 25 days or if they use other courses beyond the basic course)If one or more exclusion criteria appear within the time of observation

If a participant wants to discontinue participation, this will be accepted without the need for reasons. However, the participant will be asked for potential reasons for discontinuation to document it for further analysis. The date and, if available, the reason for the withdrawal will be documented, and the participant‘s data will be destroyed.

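### Table 2 schedules randomisation before the T0 visit, so the study team can know the arm before the staff-rated baseline measures that enter the change scores

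*Protocol article*

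**What the plan says.** Study Design (Methods) describes the trial in these words: "This study will be a single-center, open-label and randomized wait-list-controlled trial". On allocation it says "Randomization is performed by the project leader by using a computer-based randomization algorithm", in a 1:1 ratio, and then "Each new participant of the study will receive a participant number that corresponds to the following treatment number". The baseline procedures come next in the text: questionnaires including the BDI-II, an interview in which an expert rates the HDRS, and heart rate, respiratory rate and blood pressure taken by a nurse. Only after these does it say "Next, participants will be informed about the study condition assignment".

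Table 2 (Study timeline) has three time columns: day -7 to 0, day 0 (T0) and day +30 (T1). Randomisation is ticked in the first, with eligibility and consent. The T0 visit is ticked in the second.

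Participants and Recruitment says that after consent is signed "it will take between 1 to 7 days until they will get scheduled for their first appointment", and presents this as time to consider taking part. It also says that a withdrawn participant's data will be destroyed.

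Data Analysis frames the hypotheses as a difference between arms in the change from baseline to T1. It covers the BDI-II, the HDRS and the physiological measures.

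**The concern.** In an open-label trial the baseline is the one measurement that can be fully protected from knowledge of the arm, simply by randomising afterwards. The schedule gives up that protection. The arm exists, and is known to at least one member of the team, before an expert scores the HDRS and a nurse takes the vital signs, one of which is a manual breath count. If that knowledge reached the person measuring, any resulting shift in the baseline value would pass into the change score. The HDRS is one of the two primary outcomes, and the vital signs are the secondary stress outcomes.

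The second consequence is loss. A person who leaves after randomisation but before T0 belongs to the randomised population and has no baseline value, so no change can be calculated. The document describes the time before the first appointment as time for reflection, so some departures then are foreseeable.

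**Working it through.** **1. The plan's own figure.** Inputs from Data Analysis: d = 0.50, alpha = 0.05, power 80%, two-sample t test.
- Normal approximation: n = 2(1.960 + 0.842)² / 0.50² = 62.8, so 63 per arm.
- Two-sided t test: 63.77, so 64 per arm, as stated.
- Dropout of 10%: 64 / 0.90 = 71.1, so 72 per arm (144 in total); or 128 / 0.90 = 142.2, so 143. The stated 140 is within 3% of either.

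The sample size reproduces, and this point does not depend on it.

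**2. Order of events.**

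| Step | Study Design text | Table 2 |
|---|---|---|
| Consent, eligibility | before randomisation | day -7 to 0 |
| Randomisation | described before the baseline procedures | day -7 to 0 |
| BDI-II, HDRS, vital signs | at baseline | T0 visit, day 0 |
| Participant told the arm | after the baseline procedures | not listed |

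Both sources put allocation ahead of measurement, so the order is not an artefact of a broken table. Seven days is an upper bound on the gap, since the column includes day 0. The 1 to 7 days in Participants and Recruitment run from consent to the first appointment, not from randomisation to T0.

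**3. Which measures are exposed.**
- HDRS, heart rate, blood pressure, respiratory rate: measured by staff, with no masking stated. Exposed.
- BDI-II: self-rated by a participant who does not yet know the arm. Not exposed unless staff disclose it.
- A participant's own decision to leave before T0: the same reasoning as for the BDI-II.

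**4. How a baseline shift carries through.** Change = T1 − baseline. If baseline is rated b too high in one arm and T1 is unaffected, the difference in mean change moves by the full b. This holds for a comparison of change scores. If baseline were a covariate instead, only the part given by the regression slope would carry over.

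**5. Illustration.** The shifts are assumptions; no such figure is in the document. Let s be the shift in SDs of the change score, with no true effect and 64 per arm. The noncentrality is s√(64/2) = 5.657s.

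| Assumed s | Noncentrality | Two-sided rejection rate at 0.05 |
|---|---|---|
| 0 | 0 | 5% |
| 0.1 | 0.57 | 8.7% |
| 0.2 | 1.13 | 20.2% |
| 0.3 | 1.70 | 39.1% |

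**6. Loss before baseline.** The plan recruits 70 per arm against 64 required, which leaves 70 − 64 = 6 per arm. If participants are not replaced, each loss between randomisation and T0 uses one of those six.

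**The case against.** The strongest reply is that the document permits early randomisation without establishing it. The first column of Table 2 is not a strict sequence: it also ticks participant characteristics and medication, while Study Design collects sociodemographic and treatment-related information at baseline. No interval from randomisation to T0 is given, and Figure 1, which might show the order, is not visible. The HDRS rater and the nurse are described separately from the project leader, and nothing says that the arm is passed to them. This stands as a limit on how large the problem may be in practice. It does not remove the problem: both the table and the text place allocation first, and neither says that the T0 raters are kept unaware of it.

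A reader might infer more from the sentence on participant numbers, namely that the project leader holds a visible list and can foresee the next arm while enrolling. The documents do not support that. They refer to a computer-based algorithm, mention no list, and do not say that the project leader enrols or rates. Consecutive numbering is also compatible with proper concealment, and concealment detail is something an article may leave to the full protocol. Foreseeable allocation is a risk that the text does not exclude, not a stated fact.

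A reader might also infer that dropout before T0 will differ by arm. Participants do not know their arm at that point, so their own decisions should not depend on it. Losses then would mainly cost numbers. The rule on withdrawal for low app use is a separate route to arm-dependent attrition and is not part of this point.

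**Conclusion.** The point holds in limited form. The scheduled order lets the arm be known within the study team before the staff-rated baseline measures of an open-label trial whose analysis compares change from baseline, and it allows participants to be randomised without a baseline. Details of concealment given elsewhere would not cure the timing, although evidence that the T0 raters had no access to the allocation would answer the rating part.

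The size of any bias cannot be derived from the document. The range of 8.7% to 39.1% rests on an assumed shift of 0.1 to 0.3 SD of the change score in one arm, no true effect, 64 per arm and a change-score comparison. It shows sensitivity and does not estimate what will happen. The self-rated BDI-II should be unaffected. The point is worth acting on because the correction is nearly free.

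**What to change.** In Table 2, move the randomisation tick to day 0, after all T0 measurements have been recorded and immediately before the participant is told the arm. Change the Study Design paragraph to match. Add one sentence stating that the HDRS rater and the nurse complete the T0 measurements without access to the allocation.

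Apply this to all remaining participants. With 30 of 140 enrolled by December 2021, 110 were still to come at that date. For those already enrolled, report the dates of randomisation and T0 and the number lost between them.

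The cost is a small scheduling change at the T0 visit, since allocation has to be obtained during the appointment, plus the amended table and paragraph. No change to the sample size is needed. The change protects the baseline only; it does nothing for ratings at T1, when the arm is known to participants.

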### Participants and Recruitment

In total, 140 patients should be recruited (70 for the intervention and control group each).

Inclusion criteria: inpatients or partial inpatients (day clinic, at least 18 years old, before discharge to ambulatory care as well as outpatients, all diagnosed with MDD according to the International Classification of Diseases. All participants must have a smartphone and be generally willing to download and use a mindfulness-based app for at least 30 days.

Exclusion criteria: Acute suicidality, dementia, acute substance dependency, psychotic, schizophrenic, or schizoaffective disorders, serious health conditions like unstable cardiovascular, heart, lung, endocrine or neurological disorders, and momentary use of Headspace.

The study will be brought to the attention of potentially eligible patients of the UPK through their health care providers at UPK and through the study flyer. If they show interest in participating, the patients will receive a document with all the required information regarding the study in order to give their informed consent. After the patients sign the form of consent, it will take between 1 to 7 days until they will get scheduled for their first appointment. This will give them an adequate amount of time to consider their participation carefully. Participants will be informed about the scope and procedure of the study. Their written informed consent will be obtained.

The participants can be withdrawn from the project for any of the following reasons:

At their own request (withdrawal of consent)In case of nonadherence to the study protocol (if participants use the app on less than 25 days or if they use other courses beyond the basic course)If one or more exclusion criteria appear within the time of observation

If a participant wants to discontinue participation, this will be accepted without the need for reasons. However, the participant will be asked for potential reasons for discontinuation to document it for further analysis. The date and, if available, the reason for the withdrawal will be documented, and the participant‘s data will be destroyed.

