### Intervention

The intervention will consist of the download and the daily use of the mobile application Headspace in addition to the TAU. The participants will use the course basics of the application, which offers 10 guided meditation sessions. The duration of each session can be done in 3, 5, or 10 minutes. The study foresees that the course will be conducted in three series. The participants will make the first cycle of the course with 3 minutes per session, the second with 5 minutes, and the last one with 10 minutes per session. The participants will do one session a day, which adds up to 30 days of using the mobile application. The patients need no previous knowledge of mindfulness exercises or meditation. The course introduces and guides the patients in and through different meditation techniques. After 30 days of using the application, the patients will be examined at T1. In addition, at T1, all participants of the intervention group will be asked for short feedback about the intervention (“comment/feedback to the app use”).

To monitor the adherence to the protocol and keep participants engaged in using the app daily, participants of the intervention group will be contacted weekly via email or phone (as they prefer) and reminded of the daily use of the app.

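### The in-study withdrawal rule carries the Headspace exclusion past randomisation, which conflicts with the app arm's required use and permits removal of controls who start the app

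*Protocol article*

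**What the plan says.** All in the Protocol article.

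- **Exclusion criteria** (Participants and Recruitment). The list ends with "endocrine or neurological disorders, and momentary use of Headspace".
- **Withdrawal grounds** (same section). The list opens with "The participants can be withdrawn from the project for any of the following reasons". One ground is nonadherence, defined as "if participants use the app on less than 25 days or if they use other courses beyond the basic course". Another is "If one or more exclusion criteria appear within the time of observation". No criterion and no arm is exempted.
- **After withdrawal** (same section). The date and, where available, the reason are recorded. The paragraph ends by saying that the participant's "data will be destroyed".
- **App arm** (Intervention). "The intervention will consist of the download and the daily use of the mobile application Headspace in addition to the TAU". Study Design says the same: "The intervention group will be required to download the mobile application Headspace and start their daily usage in addition to their TAU".
- **Control arm** (Study Design). Until T1, "the control group will not be told about the application and its use but will be held on a waitlist". The app's name is given to controls after the T1 visit.
- **Timing** (Table 2). Eligibility check and randomisation fall in the column for days -7 to 0, and T1 is at day 30.

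**The concern.** An exclusion criterion about current use of the trial's own app makes sense at entry. The withdrawal rule extends every exclusion criterion through the 30 days after baseline, and this one does not extend sensibly. It has two consequences.

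1. An app-arm participant who follows the protocol meets a withdrawal ground by using Headspace, and meets another by using it on too few days. The two statements cannot both stand as worded.
2. A control who starts Headspace meets a withdrawal ground. The other exclusion criteria are clinical states that can arise in either arm. This one is the trial treatment, and starting it is something a control does after allocation. Removing such controls takes a self-selected group out of one arm, and the remaining controls are no longer the group that was randomised.

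At stake is the comparability of the arms and, if the data-destruction sentence reaches this ground, the ability to analyse these controls as randomised at all.

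**Working it through.** **Reading the sections together.** The withdrawal list refers to participants in general, and observation runs from baseline to day 30, after randomisation. Current Headspace use is on the exclusion list. The ground therefore covers a control who starts the app and, literally, every compliant app-arm participant. The 25-day adherence ground shows that the second result is unintended. Nothing in the text shows whether the first is intended.

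**The plan's own sample size.** Inputs from Data Analysis: d = 0.50, alpha 0.05, power 80%, two-sample t test. Taken as two-sided, the exact noncentral t calculation gives 63.77, so 64 per group, as stated. With 140 randomised 1:1 and the stated 10% dropout, 70 x 0.9 = 63 per arm remain, and power at d = 0.50 is 79.5%. This is the baseline below.

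**Assumed inputs (not in the documents).**
- Share c of controls who start Headspace: 5%, 10% or 20%. Of 70 controls this is 3.5, 7 or 14.
- Difference delta between these controls and the other controls at T1: 0.5 SD.

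**Shift from removal.** With the starters included, the control mean is the mean of the rest plus c x delta. Removing them leaves the mean of the rest, so the shift is c x delta:
- 0.05 x 0.5 = 0.025 SD
- 0.10 x 0.5 = 0.05 SD
- 0.20 x 0.5 = 0.10 SD, which is 0.10 / 0.50 = one fifth of the planned effect

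The sign is open. If the starters do better than other controls, through motivation or through the app itself, removal favours the app. If people seek the app because they are doing worse, removal works against it.

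**Power.** Removal: 63 against 63 x (1 - c), with d held at 0.50. Retention: 63 against 63, with d = 0.50 x (1 - c), assuming that starters gain the full app effect and that the SD is unchanged.

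| c | n controls if removed | Power, removed | d if retained | Power, retained |
|---|---|---|---|---|
| 0 | 63 | 79.5% | 0.50 | 79.5% |
| 5% | 59.85 | 78.5% | 0.475 | 75.3% |
| 10% | 56.7 | 77.3% | 0.45 | 70.7% |
| 20% | 50.4 | 74.6% | 0.40 | 60.6% |

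Removal costs little power; retention under this assumption costs more. The case against the rule is therefore not a power argument.

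**The case against.** **Current use most naturally means use at entry.** Table 2 schedules the eligibility check only before baseline. If good sense stops the criterion from applying to the app arm later, the same reading can exempt controls. That is a fair reading and may be what was meant. It is not what the withdrawal ground says, because that ground expressly carries the exclusion criteria into the observation period.

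**Crossover is made unlikely.** A control would have to choose this one app unaided within 30 days; another mindfulness app does not meet the criterion. This stands, and it is the main reason for the low grading. It does not rule crossover out. The Introduction describes the app as free to download and accessible globally, every participant must own a smartphone and be willing to use a mindfulness app, and the trial is open-label at a single centre.

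**Withdrawal does not define the analysis set.** The wording is permissive, and the analysis set may be fixed in a statistical analysis plan that is not shown. This stands in part. The data-destruction sentence closes a paragraph about participants who choose to stop, so its reach to withdrawal by the study team is unclear. If it does reach that far, no analysis plan could restore the data.

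**Stronger readings that the text does not support.** A reader might infer:
- that the whole app arm will be withdrawn, but the adherence ground plainly presupposes app use;
- that controls who cross over will routinely be removed, but the rule only allows it and says nothing about how staff will apply it;
- that contamination will be hidden, but the reason for withdrawal is to be documented where available;
- that the bias favours the app, but its direction is unknown;
- that removal is harmful because it loses power, but retention can lose more.

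**Conclusion.** The point holds as a minor one. Two statements in the Protocol article conflict as worded: Headspace use during observation is a ground for withdrawal, and it is also the assigned treatment. The same wording permits removal of controls after randomisation on behaviour that follows allocation.

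The size cannot be established from the documents. The range of 0.025 to 0.10 SD depends entirely on an assumed 5% to 20% crossover and an assumed 0.5 SD difference, and its sign is open. With the app's name withheld until T1, the lower end or less is more likely than the upper. The stated 64 per group is correct for its inputs and is not in question.

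**What to change.** In Participants and Recruitment:

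1. Word the criterion as use of Headspace at screening, applied before randomisation only.
2. Take it out of the in-study withdrawal ground. The clinical exclusion criteria are outside this point.
3. State that a control who starts Headspace stays in follow-up, has the use recorded, attends T1, keeps their data in the trial and is analysed in the control arm.

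The edit is two or three sentences and adds no visit; the only extra item is a record of Headspace use in controls. The cost lies in interpretation: the effect is estimated with any crossover included and may be diluted. If crossover controls gain the full app effect, the effect falls to 0.475, 0.45 or 0.40 at 5%, 10% or 20% crossover, with the power losses tabulated above. The protocol should state that downside. It is worth accepting because the comparison then remains the one that was randomised.
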